### Sample size calculation

The minimum difference we wish to detect is 0.4 micromol/L serum CML (20% reduction in CML), with a standard deviation of 0.4 [39] with 5% Significance and 80% Power. This calculates as a total sample size of 18 individuals, plus 12 individuals to allow for withdrawals = 30 subjects required. Epidemiological studies have demonstrated a positive correlation between serum CML and all-cause and cardiovascular mortality, cardiovascular disease, glucose intolerance, impaired insulin secretion, renal impairment and diabetic vascular complications [40,41]. A 0.4 micromol/L increase in serum CML concentration represented a 68% increased risk for all-cause mortality over seven years in a large prospective cohort study [42].

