### Outcome measurements

The primary outcome of interest is the difference in serum AGE and AGE-precursor concentration (measured as CML and MG respectively) between experimental and control treatments. Secondary outcomes include HbA1c, insulin resistance (measured indirectly by homeostasis model assessment), antioxidant capacity (reduced glutathione), markers of oxidative stress on lipid molecules (urinary 8-isoprostanes), inflammatory biomarkers (serum IL-6, high sensitivity C-reactive protein, MCP-1, sRAGE), adhesion molecules (E-selectin), gut barrier integrity (TLR4), 24-hour urine and faecal CML and MG concentrations, faecal bacterial composition (*Bifidobacterium* spp., *Lactobacillus* spp., *Roseburia* spp., *Faecalibacterium prausnitzii* and *Akkermansia muciniphila*) and faecal short chain fatty acid concentrations. Lipid levels (serum total cholesterol, LDL, HDL, TG) and blood pressure will also be measured. Anthropometric measurements including BMI and waist circumference will be collected, in addition to comprehensive dietary and lifestyle data. Gastrointestinal side-effects will be assessed using a visual analogue scale adapted from Lecerf *et al.*[45]. The scale rates nine items including flatulence, bloating, rumbling, abdominal cramps, a global digestive tolerance score calculated from the five previous items, stool consistency, stool frequency and general well-being through disturbances in usual and professional activities as well as disturbances in personal and social activities. Items are scored on a 10 cm linear scale.

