### Statistical analysis

Outcome analyses will be undertaken on an intention-to-treat basis. Data will be presented as means ± SD. The Kolmogorov-Smirnov goodness-of-fit test will be used to test for normal distribution, and data not normally distributed will be log-transformed. Correlation analyses will be performed using the Pearson correlation coefficient. Significance of changes during the study will be assessed by comparing change of means between placebo and prebiotic treatment periods by paired sample t-tests. Trial data will be analysed using a linear mixed model design based on repeated measures to account for fixed factors such as treatment sequence (inulin – placebo vs placebo - inulin) and treatment period (intervention 1 vs intervention 2) in addition to participants as a random factor. Significant differences will be defined as a value of P < 0.05 based on two-sided tests. Any differences in physical activity levels, anthropometry, energy or nutrient intake during the course of the trial will be identified using ANOVA. Gastrointestinal symptom data obtained by visual analogue scale will be analysed using the Wilcoxon signed rank test. Effect sizes including 95% confidence intervals will be calculated for all significant outcomes. Data analysis will be performed using SPSS 20.0 software (SPSS, Chicago, IL).

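### Effect sizes with 95% confidence intervals are planned only in connection with significant outcomes, so a non-significant primary result has no planned treatment difference with interval

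*Protocol article*

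**What the plan says.** The Statistical analysis section contains one sentence on effect estimates and intervals: "Effect sizes including 95% confidence intervals will be calculated for all significant outcomes". The same section fixes what counts as significant: "Significant differences will be defined as a value of P < 0.05 based on two-sided tests". The only presentation promised without a significance condition is "Data will be presented as means ± SD".

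The Outcome measurements section names two primary variables: "The primary outcome of interest is the difference in serum AGE and AGE-precursor concentration (measured as CML and MG respectively"). Nothing exempts them from the rule. The Sample size calculation section sets the target: "The minimum difference we wish to detect is 0.4 micromol/L serum CML (20% reduction in CML"). It gives an SD of 0.4 from a cited source, a test level of 5% and power of 80%, and it concludes: "This calculates as a total sample size of 18 individuals, plus 12 individuals to allow for withdrawals = 30 subjects required". No sample-size calculation is given for MG or for any secondary outcome.

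**The concern.** Planning the estimate and interval on the strength of the P value has two consequences.

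First, if CML or MG is not significant, the plan provides no treatment difference with interval. That interval shows whether the result is merely imprecise or rules out the 0.4 micromol/L difference the trial was sized to find. The article's list of strengths presents the trial as the first on this question, so a null result would be informative only if it came with that number.

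Second, the set of effect sizes with intervals is chosen because the estimates were large relative to their error. On average such estimates overstate the truth, and the more so the lower the power. This matters most for MG and the long list of secondary markers, for which power is unknown.

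**Working it through.** **Inputs.** From Sample size calculation: target difference 0.4 micromol/L, SD 0.4, 5% significance, 80% power, 18 evaluable participants, 30 in total. From Statistical analysis: two-sided P < 0.05 and a paired comparison. The article does not say whether 0.4 is a within-person SD, a between-person SD or the SD of the paired differences.

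**Step 1: reproduce n = 18.** Read 0.4 as the within-person SD. The SD of a paired difference is then 0.4 × √2 = 0.566.
- Normal approximation: 2 × [0.4 × (1.960 + 0.842) / 0.4]² = 15.7, rounded up to 16.
- Exact noncentral t: n = 18, with power 0.807 on n − 1 degrees of freedom or 0.804 on n − 2.

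This matches the article. If 0.4 were the SD of differences, the answer would be 8 (normal) or 10 to 11 (t). A parallel-group formula gives 16 per arm, 32 in all. The within-person reading is therefore the working assumption, with the SD-of-differences reading shown as the alternative.

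**Step 2: the interval that would be available.** Half-width = t(0.975, n − 2) × SD of difference / √n.
- n = 18: 2.120 × 0.566 / √18 = 0.28 micromol/L
- n = 30: 2.048 × 0.566 / √30 = 0.21 micromol/L
- With SD of differences 0.4: 2.120 × 0.4 / √18 = 0.20 and 2.048 × 0.4 / √30 = 0.15

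At n = 18 an estimate must therefore exceed roughly 0.28 before it qualifies for an interval.

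**Step 3: what the rule leaves out and what it selects.** Trials were simulated with the estimate normal about the true difference, its standard error drawn from the matching chi-square distribution, a t-test on n − 2 degrees of freedom, and SD of difference 0.566. Inflation is the signed mean estimate among significant trials divided by the true difference.

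| True difference | n = 18: no interval | n = 18: inflation | n = 30: no interval | n = 30: inflation |
|---|---|---|---|---|
| 0.4 (design) | 20% | 1.11 | 4% | 1.02 |
| 0.3 | 44% | 1.29 | 20% | 1.12 |
| 0.2 | 71% | 1.74 | 54% | 1.43 |
| 0.1 | 89% | 2.96 | 85% | 2.48 |
| 0 | 95% | – | 95% | – |

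With SD of differences 0.4 and a true difference of 0.2, inflation falls to 1.34 at n = 18 and 1.15 at n = 30. With a true difference of 0.1 at n = 18 it is about 2.3.

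**Step 4: what a null result could have said.** With a true difference of zero, 95% of trials are non-significant. Among those, the 95% interval excludes a 0.4 reduction in about 82% at n = 18 and 98% at n = 30. With the smaller SD the interval is narrower and these shares are higher.

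**Step 5: can the interval be rebuilt from means and SDs?** For two treatments measured in the same people, the variance of the difference is SD₁² + SD₂² − 2r·SD₁·SD₂. The correlation r is not among the quantities promised, so per-treatment means and SDs do not determine the paired interval.

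**The case against.** The sentence does not contain the word *only*. It promises intervals for significant outcomes and does not say they will be withheld elsewhere. A reader might infer an outright prohibition, but the text does not go that far. What stands is that this is the article's sole provision for intervals and that it is tied to significance, so nothing is planned for the rest.

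A reader might also infer that the trial's reported effects will in general be exaggerated. The article does not support that. Means are promised for every outcome, so the point difference can be seen for null outcomes too. For CML, the one outcome with a sample-size calculation, inflation at the design effect is only 2% to 11%. The larger factors belong to true effects of 0.2 or 0.1, which are hypothetical, and they shrink if 0.4 is the SD of differences. Nor would changing the rule alter the estimate for any one significant outcome: it ends the selection of what is shown, not the overestimation that comes with having passed the threshold.

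Finally, one might conclude that a null trial could never say what it rules out. That is also too strong. The paired tests and mixed model would be fitted regardless of the result, so an interval could be added when the paper is written. The defect lies in what is planned, and nothing is irrecoverably lost.

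**Conclusion.** The point holds as a defect in a stated reporting rule, and it should be corrected. It does not invalidate the test. The firm part is that a non-significant CML or MG result has no planned treatment difference with interval, and the planned means and SDs cannot replace it. That interval would usually be informative: under a true null it would exclude the trial's own target in about 82% to 98% of non-significant trials, depending on whether 18 or 30 people complete. Even at the design effect, about one trial in five with 18 completers would reach no planned interval.

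The upward selection of effects with intervals is real, but its size is uncertain. It is slight for CML at the design effect and could be substantial for MG and the secondary markers, whose power is not stated. The figures for CML assume that 0.4 is the within-person SD. The alternative reading changes their size but not their direction.

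**What to change.** Replace the sentence in Statistical analysis with: *The treatment difference with its 95% confidence interval will be reported for every primary and secondary outcome, whatever its P value.*

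This ends the selective reporting and lets a null result be interpreted against the 0.4 micromol/L target. Sample size, alpha, power and data collection are unchanged, and the planned analyses already yield the intervals. The cost is one replaced sentence and slightly longer results tables.

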## Discussion

AGEs are derived from both exogenous and endogenous sources, and the rate at which AGEs accumulate in the body is dependent to a large extent on the chronological age, lifestyle and metabolic health of an individual. Smoking cigarettes and consuming foods containing high concentrations of AGEs (and their precursors) increases the accumulation of AGEs from exogenous sources. Endogenous AGE formation is accelerated under conditions of hyperglycaemia, dyslipidaemia and increased oxidative stress, conditions that are common in individuals with diabetes and in those at risk of developing type 2 diabetes (such as those with prediabetes and the metabolic syndrome) [58]. Moreover, in individuals with impaired renal function, urinary AGE excretion may be diminished resulting in a greater accumulation of AGEs in the body [59].

Risk factors for the development of type 2 diabetes include obesity, hypertension and cardiovascular disease; conditions that are commonly associated with unhealthy lifestyles including poor food habits. Restricting the intake of foods high in AGEs might potentially reduce AGE accumulation, but adherence to such diets can be challenging given that foods high in AGEs are very palatable due to their enhanced flavour, colour and aroma [60].

Supplementation of the diet with bifidogenic prebiotic fibres (such as inulin) may reduce or retard the accumulation of AGEs in individuals at risk of developing type 2 diabetes. Prebiotics have been shown to improve and restore optimal microbial balance within the gastrointestinal tract, potentially reducing AGE absorption and/or production by the human host. Preliminary investigations indicate that consuming a high-AGE diet is sufficient to favour the proliferation of potentially pathogenic colonic bacteria over more beneficial species. Consumption of glycated proteins [34], fried meats [61] and toasted wheat flakes [62] encouraged the preferential growth of greater numbers of detrimental gram negative and sulphate-reducing colonic micro-organisms when compared to control diets. Short Chain Fatty Acids (SCFAs) produced as a bacterial by-product of prebiotic fermentation act to lower the intestinal pH, inhibiting the growth of protein-degrading micro-organisms capable of producing potentially toxic metabolites. SCFAs also stimulate colonic smooth muscle contractions, speeding intestinal transit and limiting the time available for protein fermentation and putrefaction to occur in the gut [63]. Therapeutic manipulation of the gut microbiota with prebiotics may restore gut normobiosis and reduce AGE accumulation in humans at risk for type 2 diabetes development by the following mechanisms:

### Maintenance of gut barrier function

Kinetic studies have estimated that up to 30% of dietary AGEs consumed are intestinally absorbed [64]. Under circumstances of increased intestinal permeability, it is likely that greater quantities of dietary AGEs and their reactive dicarbonyl precursors may be able to gain entry into the systemic circulation. Elevated levels of circulating proinflammatory cytokines and ROS frequently observed in individuals with prediabetes are known to compromise tight junctions between cells, disrupting the integrity of the intestinal barrier and enabling the absorption of larger, potentially deleterious compounds [65]. Prebiotic fermentation products may reduce gastrointestinal permeability and as a result limit the absorption of exogenous AGEs.

The SCFAs acetate and butyrate are intricately involved in the maintenance of gut epithelial integrity. Acetate increases colonic blood flow and butyrate is the principal fuel for colonocytes, assisting to optimise epithelial cell health [66]. Butyrate reduces gastrointestinal permeability by enhancing the activation of the peroxisomal proliferator-activated receptor gamma (PPARgamma) gene, a nuclear receptor involved in the attenuation of inflammation in colonic epithelial cells [67]. Butyrate also upregulates the expression of mucin-associated genes important in maintaining the integrity of the intestinal mucosal barrier [68]. Oligofructose supplementation in mice has been shown to increase the expression of zonula and occludin, proteins important in the maintenance of tight junctions between gastrointestinal cells [69], and a dietary inulin intervention reduced markers of intestinal permeability in healthy adult males [70]. Butyrate is a histone deacetylase inhibitor and is likely to promote the transcription of these tight junction proteins. Prebiotic-induced changes in gut microbiota also increase endogenous production of Glucagon-like peptide 2 (GLP-2), which enhances gut barrier function by promoting the proliferation of crypt cells [71,72].

### Reduction of oxidative stress, inflammation and insulin resistance

Increased production of ROS stimulate endogenous AGE formation by oxidising glucose and unsaturated fatty acids to generate reactive dicarbonyls. Experimental drug treatments which attenuate oxidative stress have previously demonstrated reductions in serum AGE levels [73]. Cytokine production at sites of inflammation stimulate immune cell activation of NADPH oxidase (NOX) and production of myeloperoxidase, enzymes involved in the oxidation of amino acids to form AGE precursors [74]. Activated immune cells can also secrete the high-mobility group box 1 (HMGB-1) protein which is capable of binding to RAGE, thereby inducing further inflammation [75].

A high fat diet (independent of the level of obesity in the host) is associated with negative changes in bacterial communities within the colon [76]. In response to a high fat meal, bacterial lipopolysaccharide (LPS) translocates from the intestine into the host circulation, resulting in ‘metabolic endotoxemia’ [77,78]. LPS is a major component of the outer membrane of gram negative bacteria, and is a potent activator of the mammalian immune system. LPS interaction with immune cells stimulates macrophage over-production of ROS, enhances the secretion of pro-inflammatory cytokines, and contributes to weight gain and development of insulin resistance [79,80]. Individuals with type 2 diabetes have been found to possess endotoxemia levels 2-fold higher than people without diabetes [81]. Metabolic endotoxemia also positively correlates with total energy intake and fasting insulin levels in the general population [82]. In mice with high fat diet-induced metabolic endotoxemia, nutritional supplementation of the diet with prebiotics restored intestinal levels of gram positive bacteria (particularly Bifidobacterium species) and subsequently improved glucose tolerance and reduced circulating concentrations of LPS and pro-inflammatory cytokines [83]. Human trials involving dietary prebiotic supplementation have successfully reduced serum LPS levels [45] and markers of lipid peroxidation (a process which generates AGE precursors), possibly through the reduction of ROS production or the direct antioxidant ability of some Bifidobacterium and Lactobacillus bacterial species [84,85].

SCFAs produced as a bacterial by-product of prebiotic fermentation are absorbed into the host circulation, effecting the expression of a wide range of genes in distal tissues associated with cell proliferation, differentiation and apoptosis. SCFAs are ligands for the G-protein coupled receptors (GPRs) GPR41 and GPR43 [86] on immune cells. These receptors are involved in down-regulating inappropriate immune cell production of pro-inflammatory cytokines, chemokines and ROS [87]. The SCFAs acetate, proprionate and butyrate exhibit a variety of anti-inflammatory actions through inhibition of NFκB activation, prevention of LPS-stimulated TNFα production in neutrophils and suppression of cytokine production [31,88-90].

Numerous other immune modulating effects have been observed secondary to gut bacterial activity including the production of anti-inflammatory compounds such as polysaccharide A [91], peptidoglycan [92] and conjugated linoleic acid [93], and the induction of T-regulatory cells [26].

### Promotion of weight reduction

An energy-restricted diet resulting in weight loss has been shown to reduce serum AGE levels in overweight and obese individuals [94]. The consumption of prebiotics in human clinical trials has promoted self-reported satiety [95], weight reduction, reduced production of the orexigenic hormone grehlin and stimulated expression of the appetite-reducing hormone peptide YY (PYY) [96]. Interaction with GPR41 by the SCFAs proprionate and butyrate increases satiety [97], upregulates PYY production and modulates the expression of leptin, a hormone important in controlling energy intake and expenditure [31].

In mice, the selective growth of certain lactobacillus species in the colon reduced body fat storage through the up-regulation of fiaf (fasting induced adipose factor) gene expression and inhibition of lipoprotein lipase (LPL) [98-100]. These findings may have the potential to affect weight reduction in humans and subsequently reduce circulating AGE levels.

### Enhanced antioxidant capacity

Inulin enhances the proliferation of lactic acid producing bacteria capable of synthesising B-group vitamins, some of which have an antioxidant capacity [101]. These vitamins can be utilised by the human host to neutralise ROS. Vitamins B1 and B6 trap the carbonyl groups of highly reactive AGE precursors before they can react with proteins [102]. Some Lactobacillus and Bifidobacterium species are efficient scavengers of the lipid peroxidation product malandialdehyde, protecting the host from excessive accumulation of this toxic AGE precursor [84]. Inulin also exhibits antioxidant properties independent of altering gut bacterial growth and is able to scavenge a number of ROS, which may help to reduce lipid peroxidation in the stomach [103].

The SCFA butyrate, produced as a bacterial by-product of inulin fermentation, has been shown to increase colonic glutathione production [104]. Glutathione is an antioxidant co-factor required for glyoxalase I activity, an enzyme which degrades the AGE precursor methylglyoxyl. Increased production of ROS is also thought to deplete glutathione levels. Through the reduction of oxidative stress, prebiotics may assist in the maintainance or upregulation of the glyoxylase pathway.

### Reduction of hyperglycemia

Both transient and chronic elevations in blood glucose increase endogenous AGE generation. Activation of GPR43 in adipocytes by proprionate inhibits lipolysis and lowers glycemia in healthy individuals [105]. Butyrate has been shown to reverse diet-induced insulin resistance in animal studies [106], possibly by enhancing PPARgamma expression which increases fatty acid oxidation in muscle.

Glucagon-like peptide 1 (GLP-1) is an incretin hormone released from intestinal L-cells in response to consumption of carbohydrates and fats. GLP-1 potentiates glucose-induced insulin secretion, reducing post-prandial blood glucose levels. GLP-1 also enhances satiety and slows gastric emptying. Prebiotic feeding in rats promoted L-cell differentiation in the colon and increased GLP-1 production [107,108], probably through an increase in bacterial production of butyrate.

The consumption of inulin as a dietary supplement may also influence circulating AGE concentrations independently of its prebiotic function. High glycemic index (GI) diets and their resultant hyperglycemic effect have been shown to enhance AGE formation in healthy individuals [109]. Inulin is a soluble fibre which when consumed daily may play a role in the reduction of the GI of the diet. Many soluble fibres are known for their ability to delay gastric emptying and slow the rate of intestinal nutrient absorption, reducing the GI of the carbohydrates in the meal. Regular consumption of prebiotic soluble fibre reduces fasting and post-prandial serum glucose levels in people with impaired glucose tolerance [110] and type 2 diabetes [111].

#### Study strengths

● To our knowledge, this is the first trial to investigate the potential effects of gut bacterial modulation on advanced glycation.

● Random allocation of participants to treatment sequence and intention to treat analysis will ensure study bias is minimised.

● Double-blind crossover placebo-controlled trial.

● Dietary data will be obtained to determine dietary patterns as well as estimates of total energy intake, fat and AGE consumption.

● CML in this study will be measured using a validated ELISA method.

● Dietary AGE consumption will be estimated from an open-source food AGE database, containing AGE values obtained using validated measurement techniques.

